## Materials and methods

### Trial design

This study is a single-centre, prospective, single-blind, RCT with three parallel groups: LLLT, MET, and CTE (control) in a 1:1:1 ratio. This protocol was written in accordance with the Standard Protocol Items: Recommendations for Interventional Trials (SPIRIT) guidelines (Additional file 1). The flow of participants through the study is depicted in Fig. 1.

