### Primary outcome measure

The primary outcome measure is the shoulder function to be assessed using the Shoulder Pain and Disability Index (SPADI). It consists of 13 items divided into two subscales (5 items for shoulder pain and 8 items for shoulder disability). Each item is scored on a 0–10 numerical rating scale, where 0 denotes the best score and 10 denotes the worst score [49]. The scores of each subscale are added up and converted into a score out of 100, with higher scores indicating greater pain and disability [50]. The SPADI is a valid, reliable, and responsive measure of shoulder pain and disability [50–52]. Both the English [53] and Hausa (unpublished data) versions will be used in this study.

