### Sample size estimation

To our knowledge, no trial could be found evaluating the comparative effects of LLLT and MET among diabetic patients with frozen shoulder. However, given that the minimal clinically important difference (MCID) of the SPADI has been reported to be 8.0% points [67], the required sample size was estimated to detect a minimum difference of 8.0% (standard deviation [SD] = 10.0%) points in SPADI between the experimental groups (LLLT and MET) and control group (CTE) means post-intervention. Using the following parameters: F-test, repeated measures, between-subjects analysis of variance (ANOVA); alpha (*α*) level of 0.05; power of 0.80; effect size of 0.38 when accounting for 3 repeated measures; and correlation among repeated measures of 0.5, a total of 48 participants (16 participants per group) will be required for the trial. While anticipating an attrition rate of 25% (*n* = 12), the final sample size is 60, with 20 participants per group. Calculations were carried out using G Power 3.1.9.2 software [68].

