### Statistical analysis

All statistical procedures will be conducted using SPSS version 24.0 (IBM Co., Armonk, NY, USA) at a probability level of 0.05. Data distribution will be examined statistically using the Kolmogorov–Smirnov and Shapiro–Wilk test, and graphically using histograms, Q-Q plots, and Boxplots. The Levene test will be applied to check for homogeneity of variance. In case of skewed distribution, data transformations using log or square root transformation will be used. Continuous variables will be presented by mean and SD whereas categorical variables will be presented using frequency and percentage. Baseline comparison of continuous variables among the groups will be performed using One-way ANOVA and for categorical variables using the chi-square (χ^2^) test.

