### Statistical methods for primary and secondary outcomes

The intention-to-treat principle will be the main analysis and will be conducted by including each participant's available data according to original allocation and irrespective of the level of attendance. A mixed between–within subjects ANOVA will be used to evaluate time effect (baseline, 8 weeks, 3 months), group effect (LLLT group, MET group, control group), and group-by-time interaction effect for all outcome measures. Post hoc analysis using Bonferonni correction will be applied for pairwise comparisons for significant differences detected in the primary outcome measures. Fisher's least significant difference (equivalent to no adjustment) will be applied to the secondary outcome measures. Effect size will be computed to describe the magnitude of change in all the outcomes. Potential confounding variables such as age, gender, BMI, and duration of DM will be controlled in the main analyses.

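### Bonferroni on the three SPADI arm pairs is valid but needlessly conservative: Holm on the same comparisons gains about 3 power points per arm, 6 for both arms, at the same 0.05 limit

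*Protocol article*

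**What the plan says.** The trial has "three parallel groups: LLLT, MET, and CTE (control) in a 1:1:1 ratio", so there are three arm pairs: LLLT versus CTE, MET versus CTE, and LLLT versus MET. Testing is "at a probability level of 0.05" (Statistical analysis).

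Under Statistical methods for primary and secondary outcomes, a mixed ANOVA over baseline, 8 weeks and 3 months examines the time effect, the "group effect (LLLT group, MET group, control group), and group-by-time interaction effect for all outcome measures". For the primary outcome it continues: "Post hoc analysis using Bonferonni correction will be applied for pairwise comparisons for significant differences detected in the primary outcome measures". For the others: "Fisher's least significant difference (equivalent to no adjustment) will be applied to the secondary outcome measures".

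The section does not say which ANOVA effect opens the pairwise step, or whether pairs are compared at 8 weeks, at 3 months, at both, or on the average over time.

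The sample size section sizes the trial on the three-group F test, to "detect a minimum difference of 8.0% (standard deviation [SD] = 10.0%) points in SPADI" between the experimental arms and control.

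**The concern.** The hypothesis is pairwise: LLLT or MET does better than CTE. The SPADI pairs therefore carry the trial's main answer, but the 80% power in the sample size section belongs to the three-group F test. Power for the pairs is lower, with 16 to 20 patients per arm, so the choice of multiplicity method matters.

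Bonferroni holds every pair to 0.0167 however many pair nulls remain true. With three arms, if the means are not all equal, at most one pair can still be equal, so most of the 0.05 goes unused. A method with the same error guarantee and more power is available at no cost in patients.

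**Working it through.** **Inputs from the protocol article.** Alpha 0.05; three arms, 1:1:1; 8-point difference, SD 10; correlation 0.5; three measures; 48 evaluable (16 per arm), 60 enrolled (20 per arm). True means are taken as 8, 8 and 0, which is the configuration behind the stated effect size.

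**The plan's own figure.** The means 8, 8, 0 have grand mean 5.33 and standard deviation √[(2.67² + 2.67² + 5.33²)/3] = 3.77, so f = 3.77/10 = 0.377, against the stated 0.38. The noncentrality is λ = f²·N·m/(1 + (m − 1)ρ) = 0.38² × 48 × 3/(1 + 2 × 0.5) = 10.4. With 2 and 45 degrees of freedom at 0.05 this gives power 0.804. The 48 reproduces, for the F test only.

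**Decision rules compared, three pairs at one visit.**
- Bonferroni: each pair at 0.05/3 = 0.0167, after a significant F test.
- Holm, no gate: smallest p at 0.05/3 = 0.0167, next at 0.05/2 = 0.025, last at 0.05, stopping at the first failure.
- Closed test: three-group F test at 0.05 at that visit, then each pair at 0.05.

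**Family-wise error, 20 per arm (simulation, normal data, pooled variance).**

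| Truth | Bonferroni | Holm | Closed test |
|---|---|---|---|
| No arm differs | 0.043 | 0.044 | 0.051 |
| One arm clearly differs | 0.017 | 0.050 | 0.050 |

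The second row follows from theory. One null pair remains; Bonferroni tests it at 0.0167, while Holm reaches it at 0.05 once the two false nulls are rejected. The 0.051 is 0.05 within simulation error.

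**Power at means 8, 8, 0.**

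| Setting | Target | Bonferroni | Holm | Closed test |
|---|---|---|---|---|
| SD 10, 20 per arm | each arm vs CTE | 53% | 56% | 64% |
| | both arms | 37% | 43% | 55% |
| SD 10, 16 per arm | each arm vs CTE | 42% | 45% | 52% |
| | both arms | 26% | 32% | 43% |
| Sizing model, 16 per arm | each arm vs CTE | 61% | 65% | 72% |
| | both arms | 46% | 53% | 65% |

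The sizing model uses the average of three measures at correlation 0.5: SD = 10 × √(2/3) = 8.165.

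**What the gate contributes.** Given Bonferroni, also requiring a significant F test costs only about 0.1 to 0.4 points of power, and the 0.017 is the same without it.

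**Two visits under the planned gate.** Simulated as a mixed ANOVA with group or interaction significant at 0.05, then pairs at 8 weeks and at 3 months. Family-wise error:
- One arm differs at both visits: about 0.09 unadjusted, about 0.03 with Bonferroni over three pairs per visit.
- One arm differs at 8 weeks only: about 0.15 unadjusted, just under 0.06 with Bonferroni over three pairs per visit.
- No effect: about 0.07 unadjusted, about 0.04 with Bonferroni over three pairs per visit.

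**The case against.** ANOVA followed by Bonferroni is familiar and does not inflate error for three pairs at one visit. Being strict on the primary outcome and lenient on the secondaries is a deliberate, stated choice, and Bonferroni brings matching simultaneous confidence intervals. All of this stands. The point concerns lost power, not an error in the plan, and the gain from Holm is modest.

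A reader might infer three stronger things.

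- *That the plan corrects twice, and that the F gate and Bonferroni compound.* They do not. The 0.017 is 0.05/3 with or without the gate, and the gate costs under half a point.
- *That Bonferroni is redundant, so the pairs can go unadjusted for a gain of about 11 points per arm (53% to 64%).* This holds only for one three-group test and one set of three pairs at the same visit. The article plans a mixed ANOVA over three times and names no deciding visit, and its Discussion hypothesises superiority both after treatment and at 3 months. A significant group or interaction effect does not test equality of the three means at a given visit. If both visits are compared, Bonferroni does most of the protecting.
- *That the article misdescribes Fisher's method.* Its remark that "least significant difference (equivalent to no adjustment) will be applied to the secondary outcome measures" is a fair description of the pairwise p-values and makes no claim about error control.

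Holm has a limit too. It beats Bonferroni on the same family. If both visits are counted, the family is six, Holm starts at 0.05/6 = 0.0083, and the gains above do not carry over against Bonferroni applied to three pairs within each visit. That within-visit rule, however, does not fully hold 0.05 across the two visits.

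**Conclusion.** The point holds as a modest, avoidable loss of power on the primary comparisons. For three pairs at one visit, Bonferroni uses about 0.017 of the 0.05 once one arm truly differs. Replacing it with Holm gains about 3 points for each arm versus CTE and 6 for both arms at SD 10, whether 16 or 20 per arm are analysed. Under the sizing model at 16 per arm the gains are 4 and 7 points. Holm holds 0.05 without relying on the ANOVA gate.

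These figures assume normal data with equal variances, true means 8, 8 and 0, and one family of three comparisons. The larger gain of the closed test depends on a fixed visit and a matching gate, neither of which the article provides.

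**What to change.** In Statistical methods for primary and secondary outcomes, replace Bonferroni with Holm for the SPADI comparisons, and define the family as all arm pairs at all visits that will be tested (three for one visit, six for both post-baseline visits).

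A closed test is an acceptable alternative only if two things are written in first: a single deciding visit, and a three-group SPADI test at that same visit as the gate, in place of the mixed-ANOVA group or interaction effect. The three pairs may then each be tested at 0.05. Unadjusted pairs after the planned mixed ANOVA at both visits should not be used.

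The Holm change costs one sentence and no patients. SPSS already prints the unadjusted p-values; for three pairs, Holm compares them in ascending order with 0.0167, 0.025 and 0.05. The downside is that matching simultaneous confidence intervals are less direct than with Bonferroni, so ordinary 95% intervals should be reported beside the Holm decisions and labelled as unadjusted.

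### Baseline SPADI is a level of time in the primary ANOVA rather than a covariate, so the group effect that was powered is diluted to 5.33 of 8 points and has power 0.44, not 0.80

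*Protocol article*

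**What the plan says.** In the protocol article, the section on statistical methods for primary and secondary outcomes sets the model: "A mixed between–within subjects ANOVA will be used to evaluate time effect (baseline, 8 weeks, 3 months), group effect (LLLT group, MET group, control group"), together with the "group-by-time interaction effect for all outcome measures". Baseline is therefore one of three outcome occasions. On covariates the same section says: "Potential confounding variables such as age, gender, BMI, and duration of DM will be controlled in the main analyses". Baseline SPADI is not named as a covariate there or elsewhere in the article.

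The sample size section aims to "detect a minimum difference of 8.0% (standard deviation [SD] = 10.0%) points in SPADI" and places that difference "between the experimental groups (LLLT and MET) and control group (CTE) means post-intervention". The test it powers is "F-test, repeated measures, between-subjects analysis of variance (ANOVA"), with three repeated measures, a correlation of 0.5 among them, an effect size of 0.38, alpha 0.05 and power 0.80. The result is 48 participants (16 per group), raised to 60 (20 per group) for attrition.

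The Outcomes section has the outcome measures assessed before randomisation, so the expected group difference at baseline is zero.

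**The concern.** A group main effect over three occasions compares each arm's average over those occasions. If one occasion precedes treatment, that average mixes visits at which a treatment difference can exist with one at which it cannot. The estimated effect shrinks, and so does the power of the test on which the sample size rests.

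The plan also forgoes an inexpensive gain. A participant's own baseline score, correlated 0.5 with later scores on the plan's own assumption, can be used as a covariate to remove outcome variance. As a level of the outcome it cannot sensibly do that in the same model.

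At stake is a false negative in a trial of 60 people: a true 8-point benefit may be missed, or reported as about 5 points if the group effect is read as the treatment effect.

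**Working it through.** **Inputs.** From the sample size section: difference 8 points, SD 10, correlation ρ = 0.5, m = 3 occasions, alpha 0.05, effect size f = 0.38, N = 48 (n = 16 per arm) and N = 60 (n = 20). Assumptions added here: both experimental arms differ from control by 8 points, SD and correlation are equal across visits, the full 8 points is present at both 8 weeks and 3 months, and the four named covariates are ignored because the article gives no correlations for them. All powers come from the noncentral F distribution.

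**1. The plan's own figure.** For the between-subjects effect, λ = f²·N·m / (1 + (m−1)ρ), with 2 and N−3 df. With f = 0.38: λ = 0.1444 × 48 × 3/2 = 10.40, which gives power 0.804. N = 48 is reproduced. The effect size also follows from group means 0, 8, 8 with SD 10 (f = 0.377). This calculation needs the full 8 points in the average of all three occasions, baseline included.

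**2. The group effect with no difference at baseline.** Averaged difference = (0 + 8 + 8)/3 = 5.33 points. f falls to 0.377 × 2/3 = 0.251.
- Power is 0.44 at N = 48 and 0.54 at N = 60 with nobody lost.
- If the effect were present at 8 weeks only, power would be 0.14 at N = 48.
- N for 80% power with 8 points at both visits: 105.

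**3. The group-by-time interaction.** The sum of squared group deviations for means 0, 8, 8 is S = 42.67. The time pattern (0, 1, 1) has a sum of squared deviations of 2/3. So λ = n·S·(2/3) / (100(1−ρ)), with 4 and 2(N−3) df. At n = 16: λ = 16 × 42.67 × 0.667 / 50 = 9.10.
- Power is 0.64 at N = 48 and 0.76 at N = 60.
- N for 80% power: 66.

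**4. Follow-up scores adjusted for baseline SPADI.** λ = n·S / residual variance, with 2 and N−4 df.
- 8 weeks alone: residual variance = 100(1 − 0.5²) = 75. At n = 16, λ = 9.10; with 2 instead of 4 numerator df this gives power 0.745. At N = 60 it is 0.845. N for 80% power: 54.
- Mean of both follow-ups: residual variance = 100((1 + 0.5)/2 − 0.5²) = 50. At n = 16, λ = 13.65, power 0.90; at N = 60, 0.96. N for 80% power: 39.

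In 10,000 simulated trials at N = 48, power was 0.438 for the group effect, 0.645 for the interaction and 0.897 for the adjusted mean of both follow-ups. The average group difference was 5.32 points.

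**5. Sensitivity to the correlation, N = 48**

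| ρ | Group effect | Interaction | Adjusted, 8 weeks | Adjusted, mean of both |
|---|---|---|---|---|
| 0.3 | 0.53 | 0.48 | 0.66 | 0.86 |
| 0.5 | 0.44 | 0.64 | 0.745 | 0.90 |
| 0.7 | 0.37 | 0.877 | 0.896 | 0.97 |
| 0.8 | 0.35 | 0.975 | 0.972 | 1.00 |

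**6. Chance baseline imbalance.** At 20 per arm the SE of a pairwise baseline difference is 10 × √(2/20) = 3.16 points. In an unadjusted 8-week contrast it carries over at about ρ times its size: 0.5 × 3.16 ≈ 1.6 points.

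**The case against.** The strongest reply is that the interaction is the natural test of a treatment effect in this design, and that it is not diluted. That stands. A reader might infer that the whole primary analysis is attenuated; the article does not support this, because it also tests the interaction, and only the group main effect averages in baseline. But the sample size is built on the group effect, and at ρ = 0.5 the interaction stays below 0.80 even with all 60 retained.

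The gain also depends on what is compared. Setting 0.90 against 0.44 would pair the best adjusted analysis with the weakest planned test. Against the interaction, an adjusted 8-week contrast gains about 10 percentage points at N = 48 (0.745 against 0.643) and about 9 at N = 60 (0.845 against 0.759). The advantage is small at ρ = 0.7 and gone by 0.8.

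The covariate list is open, so baseline SPADI is not expressly excluded. This does not rescue the plan, since baseline is already an outcome level in that model. Nor does the article give any ranking of the named covariates against baseline SPADI, so nothing here rests on their being weaker.

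A reader might also take chance baseline imbalance as a bias carried in full into the follow-up contrasts. Under randomisation it is random error, already inside the contrast's standard error, and it carries over only in part. The article does not say whether the post hoc comparisons are marginal, per visit or of change, so no power figure for them is relied on.

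Finally, which effect is decisive could be settled in a statistical analysis plan that is not shown. Silence on that is not the point. The time levels and the powered test are both stated, and they do not fit the stated post-intervention difference.

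**Conclusion.** The point holds for the group main effect, as a loss of power and an attenuated estimate. The powered test shows 5.33 of a true 8 points and has power 0.44 at N = 48, or 0.54 at N = 60 without loss, against the stated 0.80. The interaction is unbiased, but reaches only 0.64 and 0.76 at the plan's correlation. Baseline adjustment does better at that correlation: 0.745 and 0.845 at 8 weeks, 0.90 and 0.96 for the mean of both follow-ups. An adjusted 8-week contrast would itself fall short of 0.80 with 48 evaluable participants.

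The figures rest on equal SDs, a common correlation of 0.5 and the full effect in both experimental arms, at both later visits except where 8 weeks is analysed alone. Type I error is not affected. The planned ANOVA is a valid but inefficient analysis whose powered effect does not match its target, so this should be fixed rather than being a fatal flaw.

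**What to change.** Analyse the 8-week and 3-month SPADI scores in a linear mixed model with group, visit, group × visit, baseline SPADI and baseline × visit, plus the covariates already listed. Name one decisive adjusted contrast: either the group difference at 8 weeks, which matches the sample size section's wording ("control group (CTE) means post-intervention"), or the mean of both follow-ups, which has more power if the effect persists. Apply the Bonferroni correction to the pairwise comparisons of that contrast, and restate the power for that test. Treat the other continuous outcomes the same way.

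The cost is analysis wording and a revised power statement. Baseline SPADI and both follow-up scores are already scheduled for every participant, so no new measurement is needed.

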### Methods for additional analyses (e.g. subgroup analyses)

We plan to conduct responder analyses for the proportion of participants attaining clinically relevant improvement (≥ 8.0% points improvement from baseline) in shoulder function (SPADI scores) [67] post-intervention and at 3 months follow-up. Participants will be dichotomised into two “improved” (≥ 8.0% points) and “not improved” (< 8.0% points). A χ^2^ test will be used for comparison of the proportion of participants attaining or not attaining clinically relevant improvement in each study arm.

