### Hypotheses

We hypothesize that patients receiving either LLLT or MET would demonstrate superior improvement in terms of shoulder function, pain intensity, shoulder ROM, interleukin 6 (IL-6), depression, anxiety, and QoL compared to those receiving CTE.

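### The responder analysis, read naturally, is an undirected three-arm chi-square that does not address whether LLLT or MET beats CTE, and its power is about half at best

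*Protocol article*

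**What the plan says.** All references are to the protocol article.

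- **Methods for additional analyses** defines a responder by "clinically relevant improvement (≥ 8.0% points improvement from baseline) in shoulder function (SPADI scores", assessed "post-intervention and at 3 months follow-up". The comparison is a chi-square: the "test will be used for comparison of the proportion of participants attaining or not attaining clinically relevant improvement in each study arm". This section mentions no pairwise table, between-arm difference or interval.
- **Hypotheses** sets each experimental arm against control: "patients receiving either LLLT or MET would demonstrate superior improvement in terms of shoulder function", compared with CTE. The Discussion repeats this for both visits.
- **Sample size estimation** aims to "detect a minimum difference of 8.0% (standard deviation [SD] = 10.0%) points in SPADI" between the experimental groups and control, with "power of 0.80; effect size of 0.38 when accounting for 3 repeated measures" and "correlation among repeated measures of 0.5". It gives no responder rate, no expected improvement on CTE and no power for the responder test.
- **Statistical analysis** sets all tests "at a probability level of 0.05".
- **Statistical methods for primary and secondary outcomes** plans a mixed ANOVA. Bonferroni pairwise comparisons follow significant differences in the primary outcome, and an effect size is promised for every outcome.

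**The concern.** The trial asks two directional questions: is LLLT better than CTE, and is MET better than CTE? A chi-square on a table of three arms by two outcomes asks whether the three proportions are all equal. Rejection does not say which arm differs or in which direction, and the test itself gives no size of difference. The Bonferroni pairwise step belongs to the ANOVA, and the text does not carry it over to the responder proportions.

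Splitting SPADI change at one cut-off with 20 per arm also discards information. CTE is an active treatment given in 24 sessions, so control patients may well improve. If they do, most participants in every arm pass 8 points and little contrast remains. Because the analysis carries the label of clinical relevance, readers may lean on it. A significant result would not identify the better arm, and a non-significant one would be weak evidence of no benefit.

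**Working it through.** **1. The plan's own figure.** Means of 0, 8 and 8 with SD 10 give f = (8 × √2 / 3) / 10 = 0.377, stated as 0.38. For the between-groups factor with three repeated measures and correlation 0.5, the noncentrality at N = 48 is 0.38² × 48 × 3 / (1 + 2 × 0.5) = 10.40. With 2 and 45 degrees of freedom this gives power 0.804. The stated 48 participants (16 per group) reproduce. This power belongs to the mean comparison, not to the responder test.

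**2. SD of change.** This is derived from the plan's inputs: √(2 × 10² × (1 − 0.5)) = 10.

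**3. Responder rates.** Assume normally distributed change, a mean improvement of m points on CTE, and m + 8 on both active arms. Then:

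- CTE rate = Φ((m − 8)/10)
- active rate = Φ(m/10)

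The article does not give m, so a range is shown.

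**4. Power of the three-arm chi-square.** Exact enumeration of three binomials, 20 per arm, 2 degrees of freedom, level 0.05:

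| CTE improvement m (assumed) | CTE rate | Active rate | Power | Mean expected count of not improved, per arm |
|---|---|---|---|---|
| 0 | 21% | 50% | 48% | 11.9 |
| 4 | 34% | 66% | 53% | 9.0 |
| 8 | 50% | 79% | 52% | 6.2 |
| 15 | 76% | 93% | 36% | 2.5 |
| 20 | 88% | 98% | 20% | 1.1 |
| 24 | 95% | 99% | 7% | 0.5 |

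The maximum is about 53%, for m between 4 and 8.

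**5. Benchmark.** For a one-way ANOVA on mean change at 20 per arm, the noncentrality is 0.377² × 60 = 8.53. With 2 and 57 degrees of freedom, power is 72% whatever the value of m.

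**6. Direction.** With true rates of CTE 70%, LLLT 90% and MET 50%, the same enumeration gives a significant result 74% of the time. MET is then 20 percentage points worse than control.

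**7. Sensitivity to the SD of change.**

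- Correlation 0.7 (SD 7.7): power 74% at m = 8, 10% at m = 20.
- Correlation 0.3 (SD 11.8): 40% at m = 8, 20% at m = 20.
- SD 20: 16% at m = 8, 9% at m = 30.

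**8. What active-versus-CTE contrasts would deliver.** At SD of change 10 and unadjusted level 0.05, exact pairwise chi-square power is 49% at m = 8 and 13% at m = 20. At 50% versus 79%, the 95% half-width for the risk difference is about 1.96 × √(0.5 × 0.5/20 + 0.79 × 0.21/20) = 0.28, or 28 percentage points.

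**The case against.** The strongest reply is that nothing confirmatory rests on this test. It is an additional analysis. The hypothesis is tested by the mixed ANOVA with Bonferroni comparisons, and the sample size concerns mean SPADI only. That stands, and it makes the point minor.

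Second, the text does not say that the table has three arms, nor does it exclude pairwise tables. The omnibus reading is the natural one but is inferred. If pairwise tests were meant, the section should say so.

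Third, a condensed article may leave interval methods and small-count handling to the statistical analysis plan that it mentions. This is fair for those details. The choice of test, however, is stated here, and it does not match the stated question.

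A reader might infer several stronger conclusions that the document does not support:

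- **That the analysis yields no estimate at all.** Arm proportions are its subject, and an effect size is promised for all outcomes. What is not specified is a between-arm difference with an interval.
- **That a true 8-point benefit would usually be missed.** At 8 points of CTE improvement, power is 52%, so significance is slightly more likely than not.
- **That most of the power is lost as a matter of course.** From 52% to 36% at 15 points is a loss of under a third. The steep fall needs about 20 points or more on CTE and an SD of change near 8 to 12, and the article gives neither figure. At SD 20 power is low throughout.
- **That Fisher's exact test is the remedy.** Under the same model its pairwise power is 37%, 22% and 5% at 8, 15 and 20 points. At a common rate of 90% or 95% its true level is 0.012 or 0.002, against 0.039 or 0.032 for the three-arm chi-square.

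**Conclusion.** The concern holds as a minor point. On its natural reading, the planned responder test is undirected and does not address whether LLLT or MET is better than CTE; it can be significant because an active arm does worse. On the plan's SD and correlation, with an 8-point advantage for both active arms and 20 per arm, its power peaks at about 53%, against 72% for mean change. It is lower if CTE patients improve substantially. The mismatch with the hypothesis needs no numerical assumption beyond the omnibus reading. The power figures rest on normally distributed change, an SD of change of 10, full follow-up of 60 participants and, for the decline, an assumed CTE improvement. The primary inference is unaffected.

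**What to change.** In Methods for additional analyses:

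- Replace the single chi-square with the LLLT-minus-CTE and MET-minus-CTE risk differences, each with a 95% confidence interval (for example Newcombe), at 8 weeks and at 3 months.
- Keep the 8-point cut-off.
- State that the responder analysis is descriptive and subordinate to the mean SPADI comparison.
- Optionally, plot the cumulative distribution of SPADI change by arm, so that the reading does not hang on one cut-off.

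The cost is a few lines of text and one table, with no new data. The downside is that the intervals will be wide (about ±28 percentage points at 50% versus 79%). The contrasts answer the stated question and show the imprecision openly, but they do not restore power, which is limited by dichotomising with 20 per arm.
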